## Abstract

**Background:**

Domestic violence (DV) prior to, and during pregnancy is associated with increased risks for morbidity and mortality. As pregnant women routinely attend antenatal care this environment can be used to offer support to women experiencing DV. We have developed a video intervention that focuses on the use of behavioral coping strategies, particularly regarding disclosure of DV experiences. The effectiveness of this intervention will be evaluated through a randomized controlled trial (RCT) and a concurrent process evaluation.

**Methods:**

All pregnant women between 12–22 weeks of gestation attending routine antenatal care at two tertiary level hospitals in Nepal are invited to participate. DV is measured using the Nepalese version of the Abuse Assessment Screen (N-AAS). Additionally, we measure participants’ mental health, use of coping strategies, physical activity, and food security through a Color-coded Audio Computer Assisted Self Interview (C-ACASI). Irrespective of DV status, women are randomized into the intervention or control arm using a computer-generated randomization program. The intervention arm views a short video providing information on DV, safety improving actions women can take with an emphasis on disclosing the violence to a trusted person along with utilizing helplines available in Nepal. The control group watches a video on maintaining a healthy pregnancy and when to seek healthcare. The primary outcome is the proportion of women disclosing their DV status to someone. Secondary outcomes are symptoms of anxiety and depression, coping strategies, the use of safety measures and attitudes towards acceptance of abuse. Follow-up is conducted after 32 weeks of gestation, where both the intervention and control group participants view the intervention video after completing the follow-up questionnaire. Additionally, a mixed methods process evaluation of the intervention will be carried out to explore factors influencing the acceptability of the intervention and the disclosure of DV, including a review of project documents, individual interviews, and focus group discussions with members of the research team, healthcare providers, and participants.

**Discussion:**

This study will provide evidence on whether pregnant women attending regular antenatal visits can enhance their safety by disclosing their experiences of violence to a trusted person after receiving a video intervention.

**Trial registration:**

The study is registered in ClinicalTrial.gov with identifier NCT05199935.

## Introduction

Domestic violence (DV) has been defined as any form of physical, mental, sexual and/or economic abuse perpetrated by an individual against another person with whom they share a family relationship [1]. DV has a broader specter of possible perpetrators compared to intimate partner violence (IPV) which is limited to the current or former partner [2]. While the intimate partner is the most common perpetrator of DV, others such as in-laws have been identified [3–5].

Women typically report a lower prevalence of violence during pregnancy compared to the violence they report having experienced 12 months prior to pregnancy and/or their lifetime exposure [5–7]. A recent systematic review on intimate partner violence in pregnancy, including 150 studies from over 50 countries reported that the global prevalence of any type of intimate partner violence in pregnancy was 25% [8]. Prevalence figures were higher in Africa (36%) than in Asia (32.1%), South (25.6%) or North America (20.4%). The lowest prevalence was reported for Europe (5.1%). When measured, emotional/psychological violence is usually the most common form of violence, followed by physical violence with the lowest rates found for sexual violence. Two recent studies in Nepal among pregnant women reported lifetime DV from 21 – 27.7% [5, 7].

DV during pregnancy has been associated with miscarriage, late entry into prenatal care, fewer antenatal visits, inadequate weight gain during pregnancy, preterm birth, low birthweight, longer postpartum hospitalization, early cessation of breastfeeding, postpartum depression, and perinatal death [9–13].

Pregnancy presents a significant opportunity to address DV, considering the regular contact in this period between women and healthcare providers [14–16]. Despite limited evidence of its efficacy, many countries have implemented routine inquiry for the experience of violence during pregnancy. However, there have been challenges in implementation of routine inquiry, including reluctance among health professionals [17]. Other barriers to asking about violence in antenatal care include lack of training, time constraints, and insufficient options for assistance and referrals following disclosure [17]. In Nepal, routine inquiry about violence in antenatal care has not been implemented.

However, Nepali health professionals have gained awareness of the problem and possible consequences of DV due to initiatives by national governments, non-governmental organizations and national and international research projects [16, 18–21]. In contrast, pregnant women attending antenatal care may lack knowledge about the scope and risks associated with DV as well as available courses of action they can take. Some women may perceive DV as normal and acceptable under certain circumstances [22].

To cope with violence, women apply both emotion-focused strategies (e.g. use of religion, placating the husband, denial, self-blaming) and problem-focused strategies (e.g. seeking support from formal institutions and social networks) [23]. One such problem-focused coping strategy is seeking social support by disclosing about the difficulties one is experiencing [23]. Studies have investigated the effect of providing pregnant women experiencing DV with problem-focused coping strategies including disclosure of violence to a trusted person [21, 24, 25]. Evidence indicates that women will use more and new coping strategies after being given information about them [21, 25].

In previous research led by our study collaboration, we carried out a pilot study in antenatal care in Nepal which informed women of the different forms that DV can take as well as safety increasing activities, using a flipchart [21]. While the results were promising, using a flipchart is time consuming and difficult to implement in routine antenatal care. Thus, in this phase of the study we have transferred the flipchart information to the format of a short video. This allows women to receive the information in private when using a headset and tablet computer and removes some barriers to health professionals providing this information, such as lack of skills. To gain high quality evidence, we are conducting a randomized controlled trial (RCT) testing the effect of the intervention video in antenatal care, the Addressing Domestic Violence in Antenatal Care Environments RCT (ADVANCE RCT). This protocol paper describes the design of the trial and provides a rationale for the elements included in the study.

## Hypothesis and objectives

The aim of the ADVANCE RCT study is to assess the effect of an intervention video in antenatal care on the use of behavioral coping strategies in relation to the experience of DV, in particular disclosing about the experience.

The null hypothesis is that there is no difference in the proportion of women who disclose someone between the women who view the intervention video compared to the women who view the control video, at baseline.

The primary aim of the process evaluation is to investigate the factors that influence the acceptability of the video intervention and the disclosure of DV. Additionally, the evaluation seeks to examine the various contexts, individual agency, and stages involved in women’s help-seeking behaviors.

## Methods: participants, intervention and outcomes

### Study setting

The study is conducted at two non-governmental hospitals in Nepal, Dhulikhel Hospital (DH) and Kathmandu Medical College (KMC). DH is a community tertiary center situated in Dhulikhel, east of Kathmandu. KMC is located centrally in Kathmandu. At DH, routine antenatal care for low-risk women is provided by nurse-midwives. The rest of the women at DH are cared for by obstetricians. At KMC all antenatal care is provided by obstetricians.

### Eligibility criteria and recruitment

All women attending routine antenatal care at DH or KMC, aged 18 or more, with a pregnancy between 12 – 22 weeks gestational age are invited to participate by study staff. Initially, women are informed that the study seeks to improve reproductive health and involves completing two questionnaires and watching a video twice. Women expressing interest to participate further are then taken to a private room where it can be safely explained that the study includes questions about violence and their formal consent to participate is requested. Consenting women participate in the study by completing a questionnaire and watching the video using an electronic tablet equipped with a headset. Women unable to read can use a data capture method known as a Color-coded Audio Computer Assisted Self Interview (C-ACASI) to give consent and complete the questionnaire, as described in our previous study [21]. All women who complete the questionnaire at the first time point (questionnaire 1) will receive a phone call around 32 weeks gestation to invite them to complete a follow-up questionnaire (questionnaire 2).

The schedule of enrollment, intervention and data collection is displayed in Fig. 1.

**Fig. 1 Fig1:**
[figure not shown]
The study flow chart

### The intervention

The intervention video is a further development from the flipchart intervention in our pilot study [21]. The video lasts a total of 7 min and starts with a presentation of what violence is. To tell the story the video uses two fictive persons who tell about their experience of violence. In this way physical, emotional and sexual violence are presented using examples. The video informs women that they are not alone in this experience. The national helpline number and shelters are mentioned. It subsequently presents the same safety promoting activities (i.e. problem-focused coping strategies) as used in the pilot study including disclosing about the experienced violence [21]. Women are told that it is not their fault that they are experiencing the violence. The list with suggested activities and number for the helpline is repeated. The video uses the drawings from the flipchart that have been animated as well as some new ones. The whole video is texted.

The control video also lasts 7 min and presents warning signs and symptoms women can experience during pregnancy that are associated with complications and risks for adverse pregnancy outcomes. This is a repetition of information provided during antenatal care sessions. Permission to use this video has been granted by MedicalAidFilms who produced it. This film was produced to raise community awareness to promote a healthy pregnancy [26]. It too uses drawings and is texted in Nepali.

All women, irrespective of randomization arm receive a leaflet produced by the Nepal Health Authorities that promote a healthy pregnancy and informs women when to contact medical services.

### The exposure

A culturally- and linguistically- relevant version of the Abuse Assessment Screen is used to measure the experience of DV [24, 25, 27]. The original Abuse Assessment Screen for DV was developed in the USA [27], and has been widely used both clinically and in research [24, 28]. The Nepalese-version of the screening tool has been validated by our team (publication forthcoming).

### Outcomes

The primary outcome is the proportion of women who disclose someone outside the research team about their experience of DV. The outcome questions are common across both questionnaires to maximize comparison of data between the two time points.

Secondary outcomes are:*Anxiety and depression*: The ten-item Hopkins Symptom Checklist (HSCL-10) is used to measure symptoms of anxiety and depression. HSCL-10 demonstrates good sensitivity and specificity for detecting mental distress and is widely used, also in the Asian region [29, 30]. Out of 10 items, 6 indicate symptoms of depression and four symptoms of anxiety. For each item the answering options range from not at all (1) to extremely (4). The rationale for measuring distress is twofold. Firstly, we presume that women hearing that violence is not their fault, that they are not alone, that it is not acceptable and that there are possible actions to be taken may become less distressed. Secondly there is the expectation that women who disclose someone about the violence will experience support and thus less distress.*Coping strategies*: The use of coping strategies will be measured using the Ways of Coping Checklist (WCCL) selecting items from the subscales measuring seeking social support (7 items), detachment (6 items) and self-blame (3 items) [31, 32]. Assessing coping strategies using similar questions has been done in Nepal in several studies [33, 34]. The response format is on a 4-point Likert scale, where 0 = does not apply and /or not used, 3 = used a great deal. We include these scales as we hope the information in the video will reduce the use of self-blame and detachment strategies and increase the use of support seeking strategies.*Safety measures*: The use of specific safety measures in relation to living with DV is measured using the list developed by McFarlane et al. (2002) which we modified to the Nepali setting in our pilot study [21, 25].*Attitudes towards abuse*: Attitudes towards acceptance of abuse will be measured using 5 questions used by the WHO [35] and national health survey in Nepal [36]. In addition will we include 6 items from the Social Acceptance of Wife Abuse Scale (SAWAS) which cover other situations and actions known to be found an acceptable reason for violence [37]. The video tells women that they are not to blame for the abuse they receive. Thus, no actions on a woman’s part justify the use of violence.

### Background and associated variables

We collect data on age, education, and income for the woman and her partner, if she has one. We also collect data on ethnicity, if they are living rurally or in a city and if they are living in a joint family or not. We also collect data on food insecurity using Household Food Insecurity Access Scale previously used in Nepal [38, 39]. Food insecure pregnant women are more likely to suffer from violence from her household members [40]. Physical activity (in relation to nutritional status) will be measured by modifying questions from the Global Physical Activity Questionnaire [41]. Suffering from violence may have led to unintended pregnancy [42] so we collect data on pregnancy intendedness using London Measure of Unplanned Pregnancy Scale [43]. These background and associated variables can potentially influence both the exposure and the outcomes.

### Sample-size

In this study we will include 2000 pregnant women. The sample-size calculation is based on the findings from the national Demographic and Health Survey in Nepal 2016 and the validation study of the Nepal Abuse Assessment Screen (N-AAS) done in preparation for this study (publication forthcoming). The most recent Nepal survey at the time of planning the study reported that, among women who had experienced physical and sexual violence, 34% had talked to someone about it [36]. The validation study showed that 12% of the pregnant women reported the experience of DV (publication forthcoming). To detect an increase of 20 percentage points from 35 to 55% in the proportion of women who talk to someone about their experience of DV, the recruitment of 240 women experiencing DV will give at least 80% power with a significance level of 5% and after a presumed 15% attrition rate. With an expected prevalence of 12% this requires the recruitment of 2000 women.

### Randomization

The randomization on a 1:1 basis will be in blocks of 16. The randomization is computer generated, by recruitment site. The randomization program is installed by an external programmer. Upon consenting to participate in the study, women will be allocated into the intervention or control group irrespective of their DV status.

### Blinding

Healthcare staff caring for the women are blinded to the allocation as long as the woman does not discuss the content of the video with them. The statistician who will perform the analyses for the outcome paper is blinded to the allocation. Women are blinded to the allocation as the recruitment room has been organized in such a way that women do not view other screens than their own. Recruitment staff, however, are not blinded to the allocation of the women and participants may consult them about their own situations and require referrals.

### Process evaluation

The process evaluation will involve various participants, including 20–25 women who took part in the RCT, approximately 24 healthcare providers through Focus Group Discussion (FGD) and health managers from the gynecology and obstetrics departments. Additionally, interviews will be conducted with research assistants and doctoral researchers who are involved in the study following the guidelines of the Medical Research Council (MRC) framework [44] which includes considerations such as adaptations, reach, fidelity, and dosage.

The main outcome of the process evaluation is an assessment of the acceptability of the video intervention, specifically investigating the various factors that influence acceptability, such as the time required to explain and watch the video and safety considerations for the women involved. Additionally, the process evaluation will explore the factors that impact women’s disclosure of DV. This includes exploring their agency in seeking help, the relevance of the intervention content in facilitating effective assistance, and the different stages they experience during the process of seeking support for DV.

## Methods: data collection, management, and analysis

### Data collection

Participants who provide consent will complete a questionnaire using an electronic tablet. The questionnaire design has been adapted to accommodate and support women who have reading difficulties. The C-ACASI method enables women to listen to the questions and provide color-coded answers [45, 46]. For women who do not require this assistance, they have the option to read and answer the questionnaire directly without listening to the questions, which can expedite the process for them. Women complete one questionnaire at baseline (Q1) and one approximately 10–26 weeks later (Q2). For completing the follow-up questionnaire, women will receive a phone call from the research assistant to confirm their previous participation in the study and extend an invitation for a second time during their regular antenatal visit. Additionally, research assistants will gather data from the patients’ obstetric notes, including both the antenatal card and hospital register.

### Analysis

A detailed statistical analysis plan (SAP) will be developed.

The main outcome is measured by comparing the proportion of women in the intervention and control groups who have told someone about the violence they have experienced. The comparison will be presented as risk ratios with 95% confidence intervals. In addition, we will collect data on whom the woman has told about the violence and will present this as descriptive findings. A detailed description of the analysis strategy for the secondary variables will be provided in the SAP. Briefly, binary outcomes will be compared between intervention arms using risk ratios, and continuous secondary outcomes will be compared using linear mixed models to take into account the baseline values of each outcome variable. Non-parametric analysis or alternative regression models will be considered where the assumptions for the linear regression models are not met.

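### The primary outcome has no start point and the primary analysis makes no stated use of baseline disclosure, which can pull the risk ratio toward 1 and lose precision

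*Protocol article*

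**What the plan says.** Outcomes defines the primary outcome as the proportion of women who disclose their DV experience to someone outside the research team, with no time window. It adds: "The outcome questions are common across both questionnaires to maximize comparison of data between the two time points". Disclosure status is therefore known at entry.

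Analysis describes the primary comparison as "comparing the proportion of women in the intervention and control groups who have told someone about the violence they have experienced", presented as risk ratios with 95% confidence intervals. Baseline values are named once, for the linear mixed models of the continuous secondary outcomes. A detailed SAP is announced.

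Sample-size plans for 35% against 55%. The control rate rests on a national survey in which, "among women who had experienced physical and sexual violence, 34% had talked to someone about it". It states that "the recruitment of 240 women experiencing DV will give at least 80% power" at the 5% level, "after a presumed 15% attrition rate", and then: "With an expected prevalence of 12% this requires the recruitment of 2000 women".

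The opening of the Discussion gives the question as whether women experiencing DV are more likely to disclose once they have seen the intervention video. Data collection puts Q2 about 10 to 26 weeks after Q1.

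**The concern.** The outcome as worded and the stated aim are not the same quantity. A woman who had already confided in someone before enrolment has told someone, whichever video she sees. If she counts, she adds a success that the video could not have produced. Such women are expected in equal shares in both arms, so they raise both proportions and push their ratio toward 1. They also add variance to an unadjusted comparison, although the Q1 answer that would remove most of it is already collected.

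The planning rate has the same ambiguity. The survey figure describes women who had talked to someone, without any trial contact. It fits an ever-told outcome more naturally than disclosure in the weeks after a video. The trial expects only about 204 evaluable women with DV out of 2000 recruited, so precision matters.

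**Working it through.** **Inputs from the article.** 240 women with DV, 15% attrition, 1:1 allocation, 35% against 55%, 5% level (two-sided assumed, since sidedness is not stated).

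**The plan's own figure.** 240 × 0.85 = 204 evaluable, or 102 per arm. The pooled two-proportion formula without continuity correction gives power

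Φ{[0.20·√102 − 1.96·√(2·0.45·0.55)] / √(0.35·0.65 + 0.55·0.45)} = 82.4%.

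Also 240 / 0.12 = 2000. The stated figures reproduce.

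**What entry disclosure does.** Let *b* be the share who had told someone at Q1, and *c* and *t* the new-disclosure rates in the control and video arms among the rest. Assume that women who had told someone at Q1 always count at Q2. Then:

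- ever-told proportions: P0 = b + (1−b)c and P1 = b + (1−b)t
- difference: (1−b)(t−c)
- crude variance term: Vu = P0(1−P0) + P1(1−P1)
- variance term stratified on Q1: Va = (1−b)[c(1−c) + t(1−t)]
- Wald power: Φ(difference / √(V/102) − 1.96)

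The article gives none of *b*, *c* and *t*. I take c = 10% and t = 30% (a new-disclosure risk ratio of 3.0) and vary *b*:

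| b | P0 vs P1 | Ever-told RR | Vu | Va | Crude power | Stratified power |
|---|---|---|---|---|---|---|
| 10% | 19.0% vs 37.0% | 1.9 | 0.387 | 0.270 | 83% | 94% |
| 20% | 28.0% vs 44.0% | 1.6 | 0.448 | 0.240 | 68% | 91% |
| 30% | 37.0% vs 51.0% | 1.4 | 0.483 | 0.210 | 53% | 87% |
| 35% | 41.5% vs 54.5% | 1.3 | 0.491 | 0.195 | 47% | 84% |

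Worked line for b = 35%: the difference is 0.65 × 0.20 = 0.13. The crude SE is √(0.491/102) = 0.069 and the stratified SE is √(0.195/102) = 0.044. Power is Φ(0.13/0.069 − 1.96) = 47% against Φ(0.13/0.044 − 1.96) = 84% (unrounded SEs used).

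**Imperfect repeat answers.** Suppose Q2 stays at 35% against 55% and Q1 disclosure is only correlated with Q2 disclosure. The variance then falls by the factor 1 − ρ². For ρ = 0.3, 0.5 and 0.7, adjusted power is 87%, 92% and 98%, against 83% unadjusted (unpooled formula). A gain remains without perfect carry-over.

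**Does new disclosure among controls break the power statement?** Keep the 20-point difference at 102 per arm and let the control rate rise (pooled formula): 38.25% vs 58.25% gives 82%, 41.5% vs 61.5% gives 82%, 48% vs 68% gives 83%, and 54.5% vs 74.5% gives 85%. Power does not fall.

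**Why the planning rates need a definition.** If 35% vs 55% is read as new disclosure only among women who had not told anyone at Q1, and b = 35%, about 0.65 × 102 = 66 women per arm remain and power is 64%. Read as a proportion of all 102 women with DV per arm, it is 82.4%.

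**The case against.** Much of this is silence rather than a stated choice. The recall period of the disclosure question is not shown, and the aim is worded as disclosure after the video, so the questionnaire may already ask about the period since Q1. Nothing says that the primary risk ratio is crude; a risk ratio can be adjusted, and covariates are commonly left to the SAP. Asking the same questions twice suggests that Q1 is meant to be used. All of this stands against saying that the plan *does* count earlier disclosures or *does* discard Q1. It does not remove the point. The outcome definition is stated in the article and carries no date. The one mention of baseline values concerns other outcomes, and the analysis detail deferred to the SAP is expressly that for the secondary variables.

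A reader might infer that about a third of women with DV are disclosers at entry. The 34% comes from survey respondents with physical and sexual violence, while DV here is measured by the Nepalese Abuse Assessment Screen, so the entry rate is unknown.

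A reader might also infer that 80% power requires no new disclosure among controls. It does not: power stays at 82% to 85% if the 20-point difference is kept. It drops to 49% at 41.5% vs 55%, but only because holding the video arm at 55% shrinks the effect to 13.5 points. That is a different assumption about effect size.

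Finally, the gain depends on chosen inputs. Restricting the analysis to 66 women per arm without disclosure at Q1 gives 83% power at 10% vs 30%, but 71% at 20% vs 40%.

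**Conclusion.** The point holds as a weakness in the definition and efficiency of the primary analysis. As worded, disclosures from before the video can count, which does not match the stated aim, and no use of Q1 disclosure is provided for in the primary comparison. Entry disclosure is balanced by randomization in expectation, so there is no bias in the test of no effect and no excess of false positives.

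The size rests on assumptions: 10% to 35% disclosed at entry, 10% vs 30% new disclosure, 102 per arm, and entry disclosers still counted at Q2. On these, crude power is 83% down to 47% and stratified power 94% down to 84%, while a new-disclosure risk ratio of 3.0 shows as 1.9 down to 1.3. Stratification gains power at every entry rate tried. The sample-size arithmetic itself is sound; what it lacks is a statement of which outcome it describes.

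**What to change.** Before unblinding, in the protocol and SAP:

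1. Define the primary outcome as telling someone outside the research team between Q1 and Q2, and report the ever-told proportion descriptively. This addresses the dilution.
2. Keep the randomized comparison among women with DV and adjust the primary risk ratio for Q1 disclosure (yes/no), for example by modified Poisson regression with robust standard errors or by standardization. This addresses the precision. Adjustment alone would not undo the dilution of a marginal ever-told ratio, so both steps are worth taking.
3. State in Sample-size which definition and which denominator 35% vs 55% refer to. Note that the 34% behind the control rate describes having talked to someone, among survey respondents with physical and sexual violence. No statement about zero new disclosure in controls is needed.

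The cost is wording. Adjustment uses data already collected. Dating the outcome needs at most one added Q2 item, if the present question does not already fix the period. Women who have completed Q2 without that item would have to rely on the existing question and the Q1 adjustment.
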